**Patient reported indicators:**

- Generic PROM index score: PROMIS PROPr is a preference-based score which combines seven PROMIS domains of health status into one score (cognitive function, depression, fatigue, pain, physical function, sleep, social roles)
- Disease-specific PROM index scores for each chronic disease

Asthma: Asthma Impairment and Risk Questionnaire (AIRQ) score

COPD: Clinical COPD Questionnaire (CCQ) score

Diabetes: Problem Areas in Diabetes (PAID-5) score

Coronary artery disease: Seattle Angina Questionnaire (SAQ-7) score and Rose Dyspnea Scale (RDS) score

- PREM index score: Responsiveness of the health care system
- Looked at PRO feedback
- Comprehensibility of PRO feedback
- Helpfulness of PRO feedback
- Emotional reaction to PRO feedback
- Discussion of PRO feedback with physician(s)
- Health behavior in five dimensions:

Physical activity

Nutrition

Tobacco consumption

Alcohol consumption

Sleep duration

- Plans to change health behavior in the future
- Trigger for health behavioral change
- Overall health improvement
- Disease-specific health improvement

**Patient reported demographic information:**

- Age: continuous variable in years measured as dates (DD/MM/YYYY)
- Gender: categorical variable (male, female, diverse, I do not want to say)
- Height: continuous variable measured in cm
- Weight: continuous variable measured in cm
- Education: categorical variable (without general school certificate, primary or secondary school, university entrance qualification, bachelor’s degree, master’s degree, doctorate, other)
- Occupation: categorical variable (Self-employed, employed (full-time, part-time, mini job), student, apprentice, unemployed (jobseeker, homemaker, unable to work due to illness, retired), other)
- Household income: categorical variable (<749€, 750 – 999€, 1,000 – 1,499€, 1,500 – 1,999€, 2,000 – 2,499€, 2,500 – 3,499€, 3,500 – 4,499€, 4,500 – 5,499€, >5,500€, I do not want to say, I do not know)
- Household size: categorical variable (1, 2, 3, 4, 5, 6 or more)
- Household size under 14 years: categorical variable (0, 1, 2, 3, 4, 5 or more)

**The secondary data, retrieved from the participating health insurance BARMER includes the following data points:**

- Personal data: age, sex, death date (if applicable), insurance times, region of residence
- Disease management program participation: program type, participation times
- Outpatient care data: date of attendance, invoiced fee schedule items, practitioner’s specialty, diagnoses (ICD-10-GM), procedures (OPS)
- Prescriptions of medications: drug identifier, no of prescriptions, date of prescription, prescribing practitioners’ specialty, anatomic-therapeutic-code (ATC), dosage (defined daily dosage - DDD), costs
- Allied health professions (podiatric, dietary, speech and language, ergo- and physiotherapy): date of prescription, indication, diagnosis (ICD-10-GM), prescription type, remedy type, first/last date of remedy application, number of applications, prescribing practitioners’ specialty, costs
- Assistive technology: date of prescription, unique identifier of assistive technology, first/last date of application, number of applications, prescribing practitioners’ specialty, costs
- Inpatient hospital stays: clinic identifier, date of admission/discharge, admission/discharge mode, discharging departments’ specialty, diagnoses (ICD-10-GM), procedures (OPS)
- Hospital care: clinic identifier, date of entry/discharge, diagnoses (ICD-10-GM), procedures (OPS), fee schedule items, costs
- Work incapacitation: first/last date of work incapacitation, diagnosis (ICD-10-GM), days of wage-replacement-benefits, costs of wage-replacement-benefits
- Transportation: prescribing practitioner with specialty, prescription date, first/last day and number of service(s), fee schedule items, costs
- Household assistance: prescribing practitioner, prescription date, first/last day and number of service(s), fee schedule items, costs
- Short-term nursing care: prescribing practitioner, prescription date, first/last day and number of service(s), fee schedule items, costs
- Rehabilitation: prescribing practitioner, first/last day of rehabilitation, type of rehabilitation (inpatient/outpatient, mobile, combinations), funding agency, diagnoses (ICD-10-GM), costs
- Long-term care benefits: level of care, first/last date of the current level of care, care type, first/last date of care benefits, costs

1. Populations of Analysis

All patients who were selected in the identification of study population and participated in the study except for patients who are excluded from the study due to:

- Consent withdrawal

All the analyses will be performed on this population.

1. Outcome Variables
   1. PRIMARY OUTCOME

The primary endpoint of the study is the sufficient study participation to determine the representativeness of results for first, regular and full responders (compare figure 3).

[figure not shown]

*Figure 3: Overview of patient and participant segmentation*

As expected, study participation will vary depending on gender, age, and diagnosis, but this can be compensated for by weighting the study participants according to structural information on the target population. Within our study, data on healthcare utilization is available for participants and the whole BARMER population. Weighted measures of health care utilization from participants will be compared with measures of health care utilization of the complete target and will be assumed to be formally representative if the weighted measures from participants fall within the 95% confidence interval of the same measures based on data of the complete target population.

- 1. SECONDARY PARAMETERS OUTCOMES

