**Main research question:**

Can digital PROMs (ePROMs) and digital PREMs (ePREMs) be used in patients with chronic diseases for quality measurement at the health system level (e.g., for health-system performance assessment (HSPA))?

- How representative are response rates in patients with chronic diseases via digital surveys?
- How do response rates and willingness to respond multiple times vary over time by age, gender, indication, city/state, health system use (frequent versus infrequent users), web- or app-based surveys, and Disease Management Program (DMP) participation?

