**For the primary research question:**

As secondary outcome for the primary research question, (1) the response rates overall and per patient subgroups based on disease area, patient characteristics (gender, age, disease), DMP participation, and others as well as (2) the representativity of responding participants over time. For these analyses, the study population is segmented in:

- All patients: Full BARMER-insured population with at least one of the chronic diseases included in the study
- Invited patients (from “All patients”): Patients that receive the initial invitation letter
- First responders (from “Invited patients”): Patients that complete the first survey period
- Regular responders (from “First responders”): Patients that complete at least three out of four survey periods
- Full responders (from “Regular responders”): Patients that complete all four quarterly survey periods

Variables that will be analyzed in all segments:

- Age
- Gender
- Type of chronic disease
- DMP participation

For all responder groups, additional variables from survey data will be analyzed:

- Body-Mass-Index (BMI), calculated by height & weight
- Education
- Profession
- Household size
- Household income

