**Primary Outcomes**

*Sufficient response rates for representativity of subgroups*

As expected, study participation will vary depending on gender, age, diagnosis, and healthcare utilization, but this can be compensated for by weighting the study participants according to structural information on the target population.

Within our study, data on the above-mentioned patient characteristics is available for both participants and the whole target population. Weighted measures from participants will be compared with measures of the complete target and will be assumed to be formally representative if the weighted measures from participants fall within the 95% confidence interval of the same measures based on data of the complete target population.

The general methodology (see 5.1) will be applied for the analysis of the primary outcomes.

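### Representativeness of regular and full responders is judged without any PROM/PREM score, although period-1 scores exist for all first responders, and 4.1 and 5.2 differ on whether utilization is a check or also a weight

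*Protocol*

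**What the plan says.** The main research question in 1.1 is: "Can digital PROMs (ePROMs) and digital PREMs (ePREMs) be used in patients with chronic diseases for quality measurement at the health system level". Section 4.1 sets the endpoint: "The primary endpoint of the study is the sufficient study participation to determine the representativeness of results for first, regular and full responders".

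The pass rule appears twice, in different forms.

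- **Section 4.1.** On weighting: "study participation will vary depending on gender, age, and diagnosis, but this can be compensated for by weighting the study participants". On the comparison: "Weighted measures of health care utilization from participants will be compared with measures of health care utilization of the complete target". Participants' measures "will be assumed to be formally representative if the weighted measures from participants fall within the 95% confidence interval of the same measures" computed in the target population.
- **Section 5.2, Primary Outcomes.** Healthcare utilization joins gender, age and diagnosis in the sentence on weighting. The comparison is then made on that same set: "Within our study, data on the above-mentioned patient characteristics is available for both participants and the whole target population".

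Section 4.2 compares all segments on age, gender, disease and DMP status. It continues: "For all responder groups, additional variables from survey data will be analyzed". These are BMI, education, profession, household size and household income. The PROPr, disease-specific PROM and PREM scores are not listed. The same section defines first responders as those who complete survey period 1, so their period-1 scores are on file whether or not they continue.

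**The concern.** The verdict is meant to support using ePROM and ePREM results for system-level quality measurement, but no ePROM or ePREM score enters it. If people in worse health, or less satisfied with their care, are more likely to stop answering, the averages among regular and full responders drift from those of everyone who started. Demographic and claims variables capture this only in part. PREM scores in particular may have little link to utilization.

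For drop-out after the first survey the study already holds the direct evidence, namely the period-1 scores of those who left. The plan does not list it for use. What is at stake is whether a finding of representativeness for regular and full responders can be carried over to their PROM and PREM results.

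**Working it through.** **1. The plan's own funnel (section 2.5).** Inputs: 200,000 invited, 30% initial response, two-thirds allowing follow-up contact, 40% of these completing all follow-ups.

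- First responders: 200,000 × 0.30 = 60,000
- Follow-up contact allowed: 60,000 × 2/3 = 40,000
- Full responders: 40,000 × 0.40 = 16,000, which reproduces the stated figure
- First responders who do not become full responders: 60,000 − 16,000 = 44,000, and 44,000 / 60,000 = 73%

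**2. Inputs to the verdict.**

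| Place | Named for weighting | Compared |
|---|---|---|
| 4.1 | gender, age, diagnosis | utilization |
| 5.2 | gender, age, diagnosis, utilization | the same four |
| 4.2 segments | – | age, gender, disease, DMP; in responders also BMI, education, profession, household size, income |

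No row contains a PROM or PREM score. Under 5.2 a variable in the weights is also the variable checked, so agreement on it says little.

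**3. Size, under assumptions the protocol does not give.** Standard-normal PROM score (higher = better). Correlation with utilization −0.2, −0.3 or −0.5. Logistic selection at each step (30%, 2/3, 40%) with log-odds of continuing 0.2 to 0.5 per SD of PROM. Two cases: post-stratification on 50 utilization bins (5.2 reading), and no utilization in the weights (4.1 reading; age, gender and diagnosis are not modelled).

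| Correlation | 5.2 reading: weighted PROM mean, full minus first responders | 4.1 reading: utilization gap, full responders vs target |
|---|---|---|
| −0.2 | about 0.18–0.39 SD | 0.06–0.15 SD |
| −0.3 | about 0.17–0.38 SD | 0.10–0.23 SD |
| −0.5 | about 0.14–0.33 SD | 0.16–0.37 SD |

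Under the 5.2 reading weighted utilization matches the target almost exactly (about 0.001 SD at −0.3), so the check on utilization sees nothing.

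Under the 4.1 reading the gaps can be set against the half-width of the target's 95% interval. With the 200,000 invited as target this is 1.96 / √200,000 = 0.0044 SD, and it is narrower for a larger target. The rule would flag all of these gaps. A flag would not be specific, though: a perfectly unbiased sample of 16,000 has standard error 1 / √16,000 = 0.0079 SD and passes one unweighted measure with probability 2Φ(0.0044/0.0079) − 1, about 42%.

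**4. How much of the bias can be tested.** At correlation −0.3 the weighted PROM mean of full responders is off by 0.29–0.68 SD from the target. Of this, 0.13–0.31 SD has already arisen between invitation and first response, where non-responders have no scores. Only the remaining 0.17–0.38 SD can be examined.

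**5. Precision of the missing comparison.** Full versus remaining first responders, unweighted: √(1/16,000 + 1/44,000) = 0.009 SD. With equal quarters per disease: √(1/4,000 + 1/11,000) = 0.018 SD. Per sub-cohort: √(1/2,000 + 1/5,500) = 0.026 SD. Against all first responders the difference and its standard error both shrink by the factor 44/60. Weighting widens the error somewhat. Shifts of the size in step 3 would be seen clearly.

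**The case against.** The best reply is that under 4.1 utilization stays outside the weights and so is a real external check. Step 3 bears this out: under the same assumptions that rule would usually fail and thereby reveal the selection. This stands. It also means that a reader may not infer from the protocol that badly biased PROM results would be declared representative. That outcome needs the 5.2 reading, or drop-out related to experience or symptoms but not to utilization, together with selection of an assumed strength.

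It is also fair that scores for people who never responded do not exist. Their absence from the comparison with the target population is a data limit, not an analysis choice, and the full 0.29–0.68 SD should not be charged to the plan. The assumptions are simple as well: one utilization measure, although the claims data in 2.6 cover many domains, and the same health slope at every step.

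Finally, the sub-questions in 1.1 are about response rates. Section 5.1 promises a summary of effects of incompleteness and unspecified sensitivity analyses, and a SAP may add an attrition comparison. But the protocol itself fixes the pass rule and the segment variables, and these promises are not part of the verdict. Imputation is ruled out for the primary question; missForest applies only to the second and third. The score averages per survey period in 5.2 mix true change with change in who answers.

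**Conclusion.** The point holds in a limited form. The verdict for first, regular and full responders rests on utilization and patient characteristics alone, and 4.2 omits the PROM and PREM scores, although period-1 scores are available for all 60,000 expected first responders, including the 44,000 not expected to become full responders. Sections 4.1 and 5.2 disagree on the role of utilization, and that decides how much the rule can see: almost nothing on health or experience through utilization under 5.2, and part of health-related drop-out under 4.1.

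If utilization is in the weights, a bias of about 0.14–0.39 SD could arise after survey 1 without the utilization check showing it. The range rests on an assumed correlation of −0.2 to −0.5 and assumed continuation log-odds of 0.2 to 0.5 per SD. It describes a risk and does not show that the results are biased.

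**What to change.** 1. Reconcile 4.1 and 5.2 so that the utilization measures used as the check are not also weighting variables.
2. In 4.1, 4.2 and 5.2, add for regular and full responders a comparison of weighted period-1 PROPr, disease-specific PROM and PREM means with those of all first responders, per disease and sub-cohort, against a tolerance set in advance. Require it before their PROM/PREM results are called representative.
3. Add period-1 scores to the weights used for later-period PROM/PREM results. Run the check in item 2 on weights that exclude these scores, or it too would pass by construction.
4. State that the step from invited patients to first responders is verified on claims variables only, so the verdict there does not extend to PROM/PREM results.

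The cost is protocol wording and a few more tables from data already collected. The representativeness claim may turn out less favourable.

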  1. INTERVENTION

In addition to filling out the survey questions at four points in time (intervention 1), all participants will receive PRO feedback as a potential nudge (intervention 2). The PRO feedback will be a pdf report sent via email and available in their study participant profile, which graphically (line charts) shows the patients’ individual generic and disease-specific health status in comparison to the individual peer group. In addition to the visual feedback, the results will shortly be explained on the same page. The description will cover whether patient-individual PRO scores are better or worse compared to the peer group, and for longitudinal values, whether patient-related changes improved or worsened. Additional details on the scores, sub-scores, and calculations are shared with the patients on the following pages of the report. Peer groups are classified according to their disease, gender, and age group. The peer group is created based on individuals who have replied to the previous survey and will only be displayed if the group consists of at least four individuals. This threshold is set by the German General Data Protection Regulation. The report refers to the patients’ physicians as the main contact to discuss the results or in case of questions.

- 1. SAMPLE SIZE

The sample is drawn stratified randomly from insured patients of one large German statutory health insurance with about 9 million insured persons (of about 73 million statutorily insured persons in total in Germany) according to their diagnosis and/or disease management program status. A one-to-one matching of participants of one DMP with non-participants of a DMP but with the same proven diagnosis according to the ICD-10-GM system is made. Further stratification criteria are age group, gender, and health system utilization.

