An initial invitation letter is sent to 200,000 insured individuals, 50,000 of each of the selected chronic conditions (about 25,000 per sub-cohort). Diabetes type 1 and type 2 are considered jointly as there is no differentiation in the selected PROMs. The patients of all chronic diseases are allocated to groups based on their participation in DMP (DMP or non-DMP group). Prior experiences suggest that around 30% of patients react to invitations to participate in research by their insurer [29-31]. Two-thirds of initial participants are expected to allow follow-up contacts and around 40% of these patients will continue participating in all the follow-up surveys after receiving reminders for each task. Therefore, after accounting for non-participants and participants with no complete survey data we expect a complete data set for 16,000 participants. However, the first research question will investigate response rates as there is no evidence on this population yet.

- 1. STUDY PROCEDURE

Eligible participants will be participating in the study for a maximum of four quarters, starting with the first access of the digital questionnaires followed by quarterly digital surveys split into several tasks. To start the survey, participants register with their study pseudonyms and share personal information, e.g., basic demographics and identification data. Each survey period contains four tasks to be completed by participants defined as sets of questions that each will take five to ten minutes to complete. The participants are invited to answer PROM and PREM surveys.
[figure not shown]

*Figure 1: Study design: Participants’ timeline and tasks*

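### The primary representativeness rule tests the participants' estimate against the confidence interval of a fully enumerated population, so its verdict follows n/N or the choice of weights, not selection bias

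*Protocol*

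**What the plan says.** Section 4.1 (Primary Outcome) makes representativeness of first, regular and full responders the primary endpoint. Participants are weighted to the target population, and the result "will be assumed to be formally representative if the weighted measures from participants fall within the 95% confidence interval of the same measures", these being computed "based on data of the complete target population". Section 5.2 repeats the criterion: the weighted measures must "fall within the 95% confidence interval of the same measures based on data of the complete target population".

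The comparison data are a full count, not a sample. Section 4.1 says that "data on healthcare utilization is available for participants and the whole BARMER population", and section 4.2 defines the widest segment as the "Full BARMER-insured population with at least one of the chronic diseases included in the study". The size of that segment is not given.

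The two sections differ on the weights. Section 4.1 names gender, age and diagnosis as the factors that weighting corrects, and utilization as what is compared. Section 5.2 adds healthcare utilization to the factors corrected, and describes the compared measures as the characteristics it has just listed.

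Neither section gives a standard error for the participants' estimate or a margin for an acceptable difference.

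**The concern.** The interval is placed around the wrong quantity. When the whole target is observed, its mean has no sampling error. If one imagines a superpopulation, its error is SD/√N, with N far above the number of participants n. The uncertainty that matters is that of the weighted participant estimate, roughly SD/√n, and the rule leaves it out. The permitted deviation therefore shrinks as the insurer's population grows, whether or not the deviation matters and however precisely the participants are measured.

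At stake is the formal verdict on the primary endpoint, because this is the only decision rule the protocol gives for it. A group with no selection bias can be declared not representative through chance alone. Under the other reading of the weights, a group can be declared representative because it was weighted to be so.

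**Working it through.** **Inputs**
- Invited: "An initial invitation letter is sent to 200,000 insured individuals, 50,000 of each of the selected chronic conditions" (section 2.5).
- Response: "Prior experiences suggest that around 30% of patients react to invitations to participate in research by their insurer" (section 2.5); then two-thirds allow follow-up contact, and 40% of these complete all follow-ups.
- N: not stated. The floor is 200,000, since that many are invited from it. The ceiling is set by "one large German statutory health insurance with about 9 million insured persons". I assume 200,000, 1,000,000 and 2,000,000.
- f: variance factor of the weighted estimator, 1 as base case. Stratification and weighting on correlated variables can lower it. Equal allocation by disease and DMP status tends to raise it.

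**The plan's own figure.** 200,000 × 0.30 = 60,000; × 2/3 = 40,000; × 0.40 = 16,000. The stated 16,000 complete data sets are reproduced. The 60,000 is an upper bound for first responders, because section 4.2 requires completion of the first survey period and not only a reaction to the letter.

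**Probability that an unbiased measure passes** (tested measure not used in the weights):
- Variance of participant mean minus target mean: f × SD² × (1/n − 1/N).
- Deviation allowed by the rule: ±1.96 × SD/√N.
- Hence P(pass) = 2Φ(1.96/√(f × (N/n − 1))) − 1. The SD cancels.

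Example, n = 16,000 and N = 1,000,000: N/n − 1 = 61.5; 1.96/√61.5 = 0.250; P = 20%.

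| Group (f = 1) | N = 200,000 | N = 1,000,000 | N = 2,000,000 |
|---|---|---|---|
| Full responders, n = 16,000 | 44% | 20% | 14% |
| First responders, n ≤ 60,000 | 80% | 38% | 27% |

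A rule that allowed for the participants' error at the 95% level would pass 95% per measure. A simulation with a skewed count variable (1,000 draws per setting) agrees: 44% and 81% at N = 200,000, and 18% and 39% at N = 1,000,000, for full and first responders.

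**Break-even.** P falls below 50% when N/n exceeds 1 + (1.96/0.6745)² = 9.44. That is N above about 151,000 for n = 16,000 and about 567,000 for n = 60,000. The latter is about 6% of 9 million.

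**Sensitivity to f** (0.7 to 2, N = 1,000,000): 24% down to 14% for full responders, 45% down to 27% for first responders. The most favourable corner for full responders (f = 0.7, N = 200,000) gives 51%.

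**Size of the allowance.** At N = 1,000,000 the rule tolerates 1.96/√N = 0.0020 SD. The 95% half-width of the difference, 1.96 × √(1/n − 1/N), is 0.0078 SD for n = 60,000 and 0.0154 SD for n = 16,000.

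**If the tested measure is in the weights.** Calibrating on a measure sets its weighted participant value equal to the target value. The difference is then zero by construction, and the rule passes whatever the selection on anything else.

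**The case against.** Four objections have weight.

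1. A reader might infer that unbiased participants will usually fail in every group. The protocol does not support that. For first responders it needs N above about 567,000, and N is not given; at N = 200,000 they would pass 80% of the time if all 60,000 completed the first period. For full responders failure is the likelier result at every N of at least 200,000 with f = 1, though f = 0.7 brings the floor case to about even.

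2. Section 5.2 can reverse the direction. With utilization among the weighting variables, the result is a trivial pass and not a false failure. This limits where the percentages apply, but it does not rescue the rule.

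3. A reader might infer that the main research question becomes unanswerable. It does not. Section 1.1 also asks how response varies by subgroup and over time, and section 4.2 plans those analyses for every segment without this rule. The tests in section 5.1 and the planned sensitivity analyses remain too, but they supply no margin and do not replace the criterion.

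4. A reader might multiply the failure rates over several measures and three responder segments. No section says that all must pass jointly, so the figures stand per measure only.

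A statistical analysis plan could add detail, but the protocol already fixes the criterion twice, and a plan that followed it would inherit the problem.

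**Conclusion.** The rule is wrong as written and needs correcting before it is used. For measures outside the weights, its verdict is driven by n/N: an unbiased measure passes 14% to 44% of the time for full responders and 27% to 80% for first responders, over assumed N from 2,000,000 down to 200,000 with variance factor 1. Fewer than 60,000 first responders would lower the second range. With the finite-population correction applied to the target, the interval has zero width and practically nothing outside the weights could pass. For measures inside the weights, the rule can pass automatically. In neither case does the formal label tell the reader whether selection bias is small. The damage is confined to that label.

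**What to change.** In sections 4.1 and 5.2, replace the criterion. For each measure, estimate the weighted participant-minus-target difference, treat the target value as fixed, and give a design-based confidence interval that includes the variance due to the weights. Call the measure representative if the whole interval lies within a pre-specified margin.

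The margin must be justified by the study's purpose. As an illustration only, take a standardised difference of 0.10 with a 90% interval and SE = √(deff/n), where deff is the design effect. An unbiased measure then passes with probability 2Φ((0.10 − 1.645 × SE)/SE) − 1. This is practically 100% at n = 16,000 for deff 1 to 2. At n = 2,000 (16,000 spread evenly over eight sub-cohorts) it is over 99% for deff 1 and 87% for deff 2. The price is that real but smaller biases are accepted: with a true bias of 0.08 SD and deff 1, the rule would still pass about 81% of the time at n = 16,000. That is why the margin needs an argument and not a convention.

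Reconcile sections 4.1 and 5.2 on the weighting variables, so that no measure under test is also weighted on, and state which population is the target and its size.

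The cost is protocol wording and the choice of a margin. No new data are needed.
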